**Table 2: Schedule of In-Person Assessments**

|                   |                                                                                                                              | Pre-treatment                                             |          | Post-treatment  |                  |                                    |                   |
|-------------------|------------------------------------------------------------------------------------------------------------------------------|-----------------------------------------------------------|----------|-----------------|------------------|------------------------------------|-------------------|
|                   |                                                                                                                              | Screening                                                 | Baseline | 3 day follow-up | 1 week follow-up | 1 month follow-up (study endpoint) | 3 month follow-up |
| Week              |                                                                                                                              |                                                           | Week 0   | Day 3           | Week 1           | Week 4                             | Week 12           |
| Visit             |                                                                                                                              | 0                                                         | 1        | 1.5             | 2                | 4                                  | 8                 |
| Informed Consent  |                                                                                                                              | X                                                         |          |                 |                  |                                    |                   |
| Diagnostics       | Demographics                                                                                                                 | X                                                         |          |                 |                  |                                    |                   |
|                   | Psych Diagnosis (CAPS month, and lifetime, SCID, and M-FAST)                                                                 | X                                                         |          |                 |                  |                                    |                   |
| Medical           | Medical History                                                                                                              | X                                                         |          |                 |                  |                                    |                   |
| Safety            | Vital Signs and Weight                                                                                                       | X                                                         | X        | X               | X                | X                                  | X                 |
|                   | Medical Laboratory* (CBC with differential, fasting glucose, electrolytes, creatinine, liver function tests, magnesium, TSH) | X (additional Lab on lipid profile, urinalysis, cortisol) |          | X               | X                | X                                  |                   |
|                   | ECG                                                                                                                          | X                                                         |          | X               | X                |                                    |                   |
|                   | Adverse Events                                                                                                               |                                                           |          | X               | X                | X                                  | X                 |
|                   | Concomitant Meds                                                                                                             |                                                           | X        | X               | X                | X                                  | X                 |
|                   | C-SSRS                                                                                                                       | X                                                         |          |                 | X                | X                                  | X                 |
| Clinical Outcomes | PTSD Symptoms (CAPS past week, past month)                                                                                   |                                                           | X        |                 | X                | X                                  | X                 |

|                |                                                  |  |   |                                              |   |   |   |
|----------------|--------------------------------------------------|--|---|----------------------------------------------|---|---|---|
|                | Self-Reports (including PCL)                     |  | X |                                              | X | X | X |
|                | Alcohol Consumption                              |  | X |                                              | X | X | X |
| Neuroendocrine | Plasma cortisol, ACTH †               |  | X | X (only plasma cortisol will be collected**) | X | X |   |
|                | Plasma mifepristone and metabolites ‡ |  |   |                                              | X |   |   |

\*Glucose, electrolytes, creatinine and liver function tests may be ordered together by requesting the comprehensive metabolic panel.

\*\*For cortisol collection at day 3, the samples will be centrifuged on site, aliquoted into labeled cryovials, and stored frozen in a deep freezer (-80 degrees Celsius) until shipped in batches to the Core Lab. In the case of a significant AE/ SAE a cortisol determination will be made at the local lab.

† The blood tubes for neuroendocrine testing (cortisol and ACTH) will be centrifuged on site, aliquoted into labeled cryovials, and stored frozen in a deep freezer (-80 degrees Celsius) until shipped to the Core Lab.

‡ Blood samples of mifepristone and its metabolites will be de-identified and labeled with participants' study ID numbers, draw date, and draw time. The blood tube will be centrifuged on site, aliquoted into labeled cryovials for 1 ml of plasma, and stored frozen in a deep freezer (-80 degrees Celsius) until shipped to MicroConstants

**Figure 3: Timeline of visits.**

[figure not shown]

#### 4.g. Treatment Adjustments

Since PTSD is a chronic disorder it is important that this study is of sufficient duration to assess the full impact of pulse treatment upon symptoms and the extent to which it is sustained; therefore, a three month study is proposed. However, since this is a placebo-controlled study, it may not be safe to delay pharmacological treatment or changes in treatment over three months in the face of increased symptoms or decreased functioning. Delaying treatment adjustments could also impact study integrity; if treatment delays led to a high number of “dropouts” it could compromise the interpretability of the study. Careful selection of participants without suicidality or a history of psychotic disorder and frequent monitoring during the trial should minimize the likelihood of treatment adjustments within the first month, and possibly throughout the

duration of the trial. Routine treatment adjustments during the 3 month treatment period will be discouraged, especially during the first month of enrollment in the study due to possible confounding impacts on the primary study endpoint. Nonetheless, should it be necessary to adjust a patient's treatment regimen during the 3 month treatment period, standard pharmacological care for PTSD will be instituted or adjusted at the discretion of the local PI. Treatment adjustments should preferentially be restricted to when there is a concern about clinical deterioration or significant decrease in functioning. Indications for treatment adjustment will include an increased potential for suicide or aggression, a significant increase in severity of PTSD or associated symptoms, or functional decline. If treatment adjustments are initiated, patients do not have to be withdrawn from the study. Careful application of the inclusion/exclusion together with the allowed use of psychopharmacology should minimize the use of treatment adjustments. The primary reasons that these medication adjustments are allowed are to prevent drop-outs of this study which can significantly harm the integrity of the study as well as to prevent bad clinical outcomes.

Instituting one of the structured psychotherapies for PTSD (e.g. prolonged exposure therapy, cognitive processing therapy) as a treatment adjustment would be problematic in so far as they can temporarily increase the severity of PTSD symptoms in some patients and can be quite effective in some patients. It would be difficult to account for these effects when interpreting the effects of mifepristone treatment. Thus, while specialized psychotherapeutic treatments are not strictly prohibited, the site PIs would need to discuss the implementation of such therapies with the Principal Proponent.

#### 4.h. Post-Treatment and Post-Study Care

All participants who exit the study prematurely during the acute treatment period will be encouraged to come in for a final termination visit for the assessment of adverse events, vital signs, and medical laboratory testing. All unused medication will be collected and sent to the study site pharmacy. The veteran will also be asked to complete a final clinical assessment three weeks after their last dose of medication. If any medical complication has arisen, an appropriate medical referral will be made. At study endpoint, the patient will be informed that the active study period has ended and that they will resume routine clinical care. To facilitate the transition, the veteran's psychiatrist or other mental health care provider will be informed about study completion and of any clinically important developments that occurred during the study. The site PI will ensure that the veteran has an adequate supply of medication until that visit and will provide care as needed until routine care is re-established. The veteran will be informed at the outset of the study that continuation on mifepristone will not be available to them after the study period ends. To preserve the integrity of the study, we will wait until follow-up on all patients is complete and then break the randomization code on all patients. A communication will then be sent to the patient informing them if they were on active treatment or placebo.

#### 4.i. Safety Monitoring

Steps taken to minimize risk include excluding veterans with major medical illnesses including adrenal insufficiency, diabetes mellitus, and a history of severe TBI. The initial health assessment will consist of a medical history and physical examination with measurement of vital signs, weight, height, and laboratory testing (complete blood cell count, fasting glucose, electrolytes, magnesium, morning cortisol, creatinine, thyroid stimulating hormone, liver function tests, lipid profile, urinalysis, and ECG). For clinical safety monitoring during the trial, complete blood cell count, fasting glucose, electrolytes, and vital signs will be measured during the 3 day follow-up and one week follow-up visits. At day 3, blood will also be collected for cortisol and stored frozen for subsequent analysis at the Core Lab, located at the James J. Peter's VA Medical Center. The day 3 cortisol sample will be analyzed in the same manner as the day 7 sample, in batches, after the participant completes all study procedures. In the event of a significant AE or SAE, a blood sample will be submitted to the local medical lab for cortisol determination, if deemed necessary by the Medical Monitoring Committee and confirmed by the Study Chair. At one week follow-up blood will also be drawn for plasma levels of mifepristone and its metabolites. Although previous studies have not found that one week of mifepristone is associated with adrenal insufficiency, because there is a theoretical risk of this, participants will be monitored for this possible adverse effect. Participants will be specifically assessed for the presence of signs or symptoms of adrenal insufficiency (malaise, fatigue, vomiting, nausea, orthostasis, hyperkalemia, hyponatremia, and eosinophilia) at baseline and at follow-up visits. All investigators will grade adverse events using version 4 of

Common Terminology Criteria for Adverse Events (CTCAE) and Common Toxicity Criteria (CTC). Common events known to be associated with mifepristone will be assessed using the reference toxicity table included in the study manual of operations to decrease the variability across investigative sites. Per the FDA's request, the investigators will explicitly inquire about the development of a rash since this is a known side effect of mifepristone. Medication will be discontinued if a rash develops or adrenal insufficiency is suspected; for the latter, a referral to internal medicine and/or endocrinology will be made. If the rash is severe or persistent, the veteran should be referred to a dermatologist.

With respect to suicidality, veterans with a history of attempted suicide within the previous two years or active suicidal ideation within the past month (participant endorses active suicidal ideation with any methods without intention to act (question 3)), as assessed by the C-SSRS, will be excluded. For all study participants, suicidality will be re-assessed at in-person post-treatment visits (one week follow-up, one month follow-up, and three month follow-up) using the C-SSRS. If the participant develops active suicidal ideation (as elicited from the C-SSRS or spontaneously reported) at any point in the study, he will be further assessed; the appropriate clinical intervention will be initiated and the local procedures for notifying the suicide prevention coordinator will be followed.

To assist in monitoring patient safety, the sites will be provided with an Investigational Brochure (IB) prepared by Corcept Therapeutics and a Drug Information Report (DIR) that is prepared and updated as needed by the pharmacy coordinating center study clinical pharmacist. The DIR provides a comprehensive review of the published literature regarding mifepristone safety data as used in the treatment of psychiatric disorders. The IB and DIR are submitted along with the protocol to the IRB, the DMC, and to the FDA as part of the IND as the safety information for the study. The statistical coordinating center then distributes the IB, DIR, protocol, and Drug Treatment and Handling Procedure manual to the study sites.

Concomitant medications will be recorded in terms of their daily dose, indication, and start and stop date. Study drug compliance will be monitored by pill counts of returned medication. In addition to the monitoring of individual patients at the local site, the study will be reviewed by the CSR&D Psychiatric, Behavioral Health & Neurologic Disorders Centralized Data Monitoring Committee.

Study participants will be monitored at each clinic visit (day 3, weeks 1, 4, and 12) and via telephone contact (weeks 2, 6, 8, and 10) by site investigators and coordinators for AEs and SAEs. Participants will be asked about any AEs or SAEs that have occurred since the previous visit or telephone contact, and vital signs will be obtained at all in-person visits. This frequent contact with participants, both in-person and via telephone, will enable site investigators to monitor safety, obtain PTSD symptom ratings, and identify any signs of deterioration. Information on all AEs and SAEs, including those related to the study intervention and those not related to the intervention, will be collected and recorded on the appropriate study event forms. All relevant information (e.g. onset of event, severity, outcome, extent to which it is or is not attributable to the drug or other study procedures) will be captured. Active monitoring of AEs and SAEs will begin as soon as a study participant signs the informed consent document and will continue through end-of-study for each participant. Instructions for contacting the VA National Suicide Hotline will be incorporated into the consent form and instructions for patients as part of safety monitoring. These safety data will be analyzed as described in the Analysis Plan (4.q.) and used to inform additional studies with mifepristone in the treatment of PTSD.

All SAEs require expedited notification, which is defined as the completion and submission of the SAE form in the Cooperative Studies Program electronic data capture (eDC) system within 72 clock-hours of a site investigator's initial awareness of an SAE. The VA Cooperative Studies Program Clinical Research Pharmacy Coordinating Center (PCC) will be responsible for evaluating all AEs for patient safety concerns. SAEs that are both related to the investigative treatment and unexpected will be reported to the FDA, CSR&D Director, and site investigators after review by the Study Chair, the PCC Director, and the CSPCC Director. The Hines CSPCC will generate tabulations of all AEs and SAEs for the Data Monitoring Committee (DMC) annually or on a more frequent schedule if requested by the DMC. The PCC will provide to the Hines CSPCC safety data coded per the Medical Dictionary for Regulatory Activities (MedDRA) for the DMC reports.

Additionally, criteria for stopping enrollment for a safety pause are to be implemented. If 30% of every projected 10 participants in either dose arm report an adverse event (possibly or definitely attributed to the study drug initiated by the site investigator) at a severity level of 3 or above, or if 20% of the projected 10 participants at a severity level of grade 4 or above, or if any occurrence of a grade 5 adverse event occurs,

participant accrual to that specific dose arm is temporarily paused until review by the Medical Monitor Committee (MMC). Events are graded as follow: 1 = mild side effect, 2 = moderate side effect, 3 = severe side effect, 4 = life threatening or disabling side effect and 5 = death. The Medical Monitor Committee (MMC) will be composed of a Hines CSPCC physician ([name]), a QA/Safety Monitor ([name]), Clinical Research Pharmacist from CSPCRPCC ([name].), Psychiatrist Consultant ([name] MD), and the Study Chair ([name]) to determine the relatedness to study drug. If the MMC agrees that the adverse events are related (possibly attributed or definitely attributed) to the study drug, further review by the DMC will be required. If the adverse event is not attributable to study drug, recruitment will continue. Hines would keep track of the rates as cases are reported in as well as review the cumulative data after every 10 cases on the study drug. If the DMC is asked to review the data, their recommendation of whether the study can proceed or not will be forwarded to the Director, CSR&D, for approval.

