#### 4.a.2. Exclusion Criteria

1. Veteran recently continued to engage in a maladaptive pattern of alcohol/substance use and/or abuse (as defined in protocol).
2. Veteran has used potent CYP3A4 inhibitors (fluconazole, ketoconazole, itraconazole, erythromycin, rifampin) and inducers within five half-lives prior to randomization.
3. Veteran is taking simvastatin, lovastatin, fentanyl, pimozide, bupropion, nefazodone, dihydroergotamine, ergotamine, quinidine, sirolimus, tacrolimus, or clarithromycin, cyclosporine, St. John's Wort, diltiazem, verapamil, propranolol, alprazolam, carvedilol or some anticonvulsants (phenytoin, phenobarbital, or carbamazepine) within five half-lives prior to randomization.
4. Veteran is taking oral corticosteroids within five half-lives prior to randomization.
5. Veteran should be free of a major medical illness and medical condition that contraindicate the administration of mifepristone. These include but are not limited to:
  - a. Veteran has a history of adrenal insufficiency or a low plasma cortisol level at screening (a.m. level less than 5 mcg/dl or a p.m. level of less than 3 mcg/dl.)
  - b. Veteran has a history of severe traumatic brain injury, a history of a stroke, or another neurological illness or injury likely to impact cognitive functioning.
  - c. Veteran has diabetes mellitus, an endocrinopathy, or another major medical illness.

- d. Veteran has a history of cardiovascular disease including a history of angina, myocardial infarction or other evidence of coronary artery disease, or congestive heart failure
  - e. Veteran has prolonged QTc interval >450 msec on ECG at screening.
  - f. Veteran has hypokalemia at screening (defined as potassium level < 3.5 mEq/L)
  - g. Veteran has a history of hepato-biliary disease or an AST, ALT greater than 2X the ULN.
  - h. Veteran has a history of renal disease or an estimated GFR of < 60 ml/min.
6. Veteran has a lifetime diagnosis of schizophrenia, schizoaffective disorder, or type I bipolar disorder.
  7. Veteran has a history of attempted suicide within the previous two years or active suicidal ideation within the past month as assessed by the Columbia-Suicide Severity Rating Scale (C-SSRS).
  8. Veteran is currently receiving specialized trauma-focused psychotherapy, such as prolonged exposure therapy and cognitive processing therapy.
  9. Veteran is not willing to use effective means of birth control during the study.

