#### 4.c. Screening and Baseline Assessment

Informed consent will be obtained prior to the initiation of study procedures utilized for the purpose of determining eligibility. In order to determine eligibility, a psychiatric and medical assessment will be performed to make a diagnostic determination regarding PTSD status and to evaluate the presence or absence of exclusionary medical and psychiatric conditions. The health assessment will consist of a medical history (including current symptoms, history of medical illness and hospitalizations, medication use), physical examination (with measurement of vital signs, weight, height), and laboratory testing (complete blood cell count, fasting glucose, electrolytes, magnesium, creatinine, thyroid stimulating hormone, liver function tests, lipid profile, urinalysis, cortisol and electrocardiogram (ECG)). Psychiatric interviews will be performed by a trained psychometrician using the CAPS and the Structured Clinical Interview for DSM-IV (SCID) in order to accurately classify PTSD and associated psychiatric comorbidities and to identify exclusionary psychiatric illnesses. Participants will also be given the OSU TBI Assessment, Columbia Suicide Severity Rating Scale (C-SSRS) (Posner et al., 2008), Miller-Forensic Assessment of Symptoms Test (M-FAST) (Veazey et al., 2005), Combat Exposure Questionnaire (CEQ), Neurobehavioral Symptom Inventory (NSI), and Trauma Assessment which will further assess their eligibility for the study. Once a participant is determined to be eligible, he will be contacted by the clinical research assistant to schedule a baseline assessment. Baseline visits will begin at 8:00AM ( $\pm$  1 hour).

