Blood samples will be obtained for the assessment of basal pre-treatment neuroendocrine activity (i.e., plasma cortisol and ACTH levels). Veterans will be called the day before their scheduled visit and asked to fast from midnight until after the blood draw. 10 ml of blood will be drawn by routine venipuncture for the determination of basal plasma cortisol and ACTH. Blood samples for hormonal analysis are collected into tubes containing ethylenediaminetetraacetic acid (EDTA), spun immediately in a cold centrifuge, and frozen for subsequent analysis. They will be shipped in batches to the Core Lab. Since observed changes in ACTH and cortisol could effectively break the blind if performed in the local hospital lab, samples will be assayed at the Clinical Neuroscience Lab at the James J. Peters VA Medical Center (Director: [name]).

Clinical assessments to be administered at the baseline visit include the CAPS, Beck Depression Inventory (BDI) (Beck et al., 1996), PTSD Checklist (PCL Military Version) (Weathers et al., 1996), National Institute on Alcohol Abuse and Alcoholism (NIAAA) Quantity and Frequency Questionnaire, State-Trait Anger Expression Inventory (STAXI) (Spielberger et al., 1988), and the Pittsburgh Sleep Quality Index (PSQI) (Buysse et al., 1989).

To address quantity and frequency of alcohol use within the last 30 days, participants will be asked to answer three NIAAA questions. This information will be obtained at baseline, 1 week follow-up, 1 month follow-up, and 3 month follow-up. Participants will be asked to report how many days per week or days per month they had at least one alcoholic beverage (defined as 1 can or bottle of beer, 1 glass of wine, 1 can or bottle of wine cooler, 1 cocktail, or 1 shot of liquor) in the last 30 days, how many drinks they consumed on average on the days in which they drank, and how many times during the last 30 days they consumed 5 or more drinks on one occasion. This measure will be used as a potential covariate to examine the effects of alcohol use on clinical outcomes.

Since grapefruit juice may increase the amount of mifepristone in blood and increase the chance of adverse events, participants will be instructed to not drink grapefruit juice while they are taking study medication.

Participants will be randomized at the end of the baseline visit, and will receive study medication.

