#### 4.d. Randomization

Prior to randomizing a patient, all screening and baseline evaluations must be completed and the patient determined to be eligible for inclusion in the study. Randomization should occur no later than two weeks from the completion of the screening visit.

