#### 4.d.2. *Randomization Procedures*

Patients determined to be eligible and willing to participate in the study will be randomly assigned to 600 mg mifepristone or placebo using a web-based randomization system with a telephone call randomization system as back-up. The clinical research assistant at the participating facility will be required to sign into this password-protected site. The clinical research assistant will enter the patient study number and will be asked to answer a few questions about eligibility in order to complete the randomization procedure. If met, the website will select the first unused entry from the pre-specified list of random treatment assignments for the particular site and then assign a randomization number, which will be used to order the double-blind treatment prescription from the study site pharmacy. The randomization lists are stored on a secure server at Hines CSP Central Study File labeled "restricted access". A copy of appropriately executed and completed consent and HIPAA authorization documents must be on file at the Hines CSPCC within 24 hours of randomization, preferably before the patient is randomized. If the internet server is down during normal business hours, the clinical research assistant can telephone the Hines CSPCC to randomize a patient.

If a participant hasn't received the study drug on the day the participant is randomized, site coordinators should make every effort to ensure the participant receives the drug within 3 days post randomization, follows the directions on how to take the drug correctly, and that no study prohibited concomitant medications are used during this period. Should the study drug assignment program be down on any business day, site coordinators will contact the Albuquerque Pharmacy Center to request an emergency manual assignment.

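### The suicidality assessment behind exclusion 7 is not repeated at the baseline visit, where participants are randomized and given drug up to 14 days after screening

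*Protocol*

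**What the plan says.** Exclusion 7 (Section 4.a.2) covers a suicide attempt in the previous two years or "active suicidal ideation within the past month as assessed by the Columbia-Suicide Severity Rating Scale (C-SSRS"). Section 4.i sets the ideation threshold at question 3 of that scale.

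The instrument is scheduled as follows:

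- **Screening.** Section 4.c: "Participants will also be given the OSU TBI Assessment, Columbia Suicide Severity Rating Scale (C-SSRS") along with other eligibility measures.
- **Baseline.** Section 4.c: "Clinical assessments to be administered at the baseline visit include the CAPS, Beck Depression Inventory (BDI"), followed by the PCL, the alcohol questions, the STAXI and the PSQI. The C-SSRS is not listed.
- **After treatment.** Section 4.i: "suicidality will be re-assessed at in-person post-treatment visits (one week follow-up, one month follow-up, and three month follow-up) using the C-SSRS".

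On timing, Section 4.c states that "Participants will be randomized at the end of the baseline visit, and will receive study medication", and Section 4.d that "Randomization should occur no later than two weeks from the completion of the screening visit".

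Section 4.d also requires, before randomization, that "all screening and baseline evaluations must be completed and the patient determined to be eligible for inclusion in the study". Under Section 4.d.2 the research assistant "will be asked to answer a few questions about eligibility in order to complete the randomization procedure"; those questions are not listed.

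**The concern.** Exclusion 7 describes a state that can change within days and ties it to one instrument, yet that instrument is last used at a visit that may precede dosing by two weeks. No section requires ideation to be assessed again before drug is given. The criterion also carries no reference date. Exclusions 2 to 4 are tied to randomization and 5a, 5e and 5f to screening, but the past-month window in exclusion 7 is tied to neither.

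The protocol leans on this criterion. Section 2.a.3 counts keeping out veterans at risk of suicide among the safeguards that make a placebo arm acceptable. Section 4.g relies on careful selection in this respect to keep treatment adjustments rare in the first month. What is at stake is patient safety at entry. The sample size and the planned analyses are untouched.

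**Working it through.** The check is a reading of the text against Table 2, with some day counting. The protocol gives no rate from which a number of affected participants could be computed.

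**1. Where the C-SSRS is scheduled**

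| In-person visit | C-SSRS in Table 2 | Text |
|---|---|---|
| Screening | yes | Section 4.c: yes |
| Baseline (randomization, drug dispensed) | no | Section 4.c list: absent |
| Day 3 | no | Sections 4.f and 4.i: not named |
| Week 1 | yes | Section 4.i: yes |
| Week 4 | yes | Section 4.i: yes |
| Week 12 | yes | Section 4.i: yes |

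The count is 4 of 6 in-person visits, and 1 of 2 pre-treatment visits. A shifted table column does not explain the blank cell: the ECG row (screening, day 3, week 1) agrees with Sections 4.a and 4.f, and the C-SSRS row agrees with Sections 4.c and 4.i. The baseline list in Section 4.c uses the verb include, which might leave room for unlisted instruments. Table 2 and the restriction in Section 4.i to post-treatment visits close that room.

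**2. Age of the eligibility assessment**

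- Screening to randomization (Section 4.d): at most 2 × 7 = 14 days. The limit is worded as a recommendation.
- Screening to receipt of drug: 14 days as scheduled. Section 4.d.2 tolerates 3 further days if drug is not received on the day, so 14 + 3 = 17 days.
- Screening to the next C-SSRS: 14 + 7 = 21 days. With late receipt it is 14 + 3 + 7 = 24 days, assuming the week-1 visit moves with the start of dosing.

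**3. How much of the exclusion window is uncovered**

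Taking a month as 30 days and the longest permitted gap, the screening C-SSRS covers the earliest 30 − 14 = 16 days of the month before randomization and leaves the last 14 uncovered. A shorter gap leaves less uncovered.

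**4. What else could catch new ideation before dosing**

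- The general eligibility condition in Section 4.d names no repeat suicidality assessment.
- The questions at randomization in Section 4.d.2 are unspecified.
- The CAPS and BDI are given at baseline. Their items are not printed, so they may touch on suicidality, but no rule uses either to re-apply exclusion 7.
- Section 4.i acts on ideation reported spontaneously, which depends on the veteran raising it.
- Adverse events are monitored from consent (Section 4.i), but the adverse-event row of Table 2 is blank at baseline.
- Exclusion 11 allows the investigator to exclude for any reason but prompts no inquiry.
- The day-3 visit (Section 4.f) reviews symptoms in person, but dosing has begun and the C-SSRS is not scheduled.

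By contrast, Section 4.i asks for signs of adrenal insufficiency to be assessed at baseline as well as at follow-up. Suicidality has no equivalent step.

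**The case against.** The strongest reply is that this is a design preference. The sections do not conflict, and the protocol settles most diagnostic and medical eligibility at screening and keeps it current with the two-week limit. The SCID, the M-FAST and the eligibility laboratory tests and ECG are not repeated at baseline to re-apply eligibility either. The screening C-SSRS still covers roughly half of the one-month window even at the longest gap, and 14 days is a maximum. For a veteran to slip through, the ideation must be new, unreported, unnoticed during a visit with a CAPS interview and a BDI, and not picked up by the eligibility questions, whose content is not shown.

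The consequence is also cushioned. Stable psychotropic medication continues, the study physician takes over psychiatric care, treatment can be adjusted without withdrawal, and an in-person review follows within 48 to 72 hours of the first dose. The protocol nowhere says that mifepristone raises suicide risk.

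Most of this stands as a limit on importance. There is no contradiction, no demonstrated harm and no estimable number affected. It does not remove the gap, because none of these provisions schedules an inquiry into suicidality between screening and the first dose. The comparison with other screening measures is also imperfect: active ideation can appear within two weeks far more readily than a lifetime diagnosis can change.

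**Conclusion.** The point holds as an inexpensive safety improvement of low priority. The instrument that defines exclusion 7 can be 14 days old at randomization, or 17 days old at receipt of drug under the tolerated delay, and no section requires it to be repeated before dosing. The reading of the schedule is secure, since the text and Table 2 agree. The clinical consequence is not quantified: how many veterans would develop unreported ideation in that interval is unknown and may be zero. The conclusion assumes that the unlisted eligibility questions at randomization do not themselves call for a repeat C-SSRS; if they do, the protocol should say so. No efficacy or safety analysis is affected.

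**What to change.** Mark the C-SSRS in the baseline column of Table 2, add it to the baseline assessments in Section 4.c, and require it to be completed and reviewed before randomization. Extend the sentence in Section 4.i on re-assessment to include baseline. In exclusion 7, state that the past-month window is judged as of randomization.

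The cost is an amendment to the schedule and wording, and a few minutes at an existing visit with an instrument the sites already give at four others. No visit or staff is added. A few veterans may fail eligibility late, after the baseline assessments have been done.
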